**Aims:**

This study was a part of a multi-center study designed to evaluate the diagnostic accuracy of  $^{99m}\text{Tc}$ -3PRGD2 imaging in lung cancer patients. The aim of this sub-topic was to compare  $^{99m}\text{Tc}$ -3PRGD2 imaging with  $^{99m}\text{Tc}$ -MDP bone scan in evaluation of bone metastasis in lung cancer patients.

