**The medical centers and facilities:**

| Centers                                                                        | SPECT system          |
|--------------------------------------------------------------------------------|-----------------------|
| The 1 st Affiliated Hospital of Fujian Medical University, Fuzhou   | GE Infinia Hawkeye    |
| Beijing Tongren Hospital, Beijing                                              | GE Infinia Hawkeye4   |
| The 1 st Affiliated Hospital of Nanjing Medical University, Nanjing | Siemens Symbia T6     |
| Peking Union Medical College Hospital, Beijing (the organizer center)          | Philips Precedence 16 |

**Estimated Enrollment:** 40

**Study Start Date:** February 2011

**Estimated Study Completion Date:** March 2014

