**Introduction:**

Integrin is mainly involved in the cell-cell and cell-matrix interactions. Integrin  $\alpha_v\beta_3$ , an important member of the integrin family, is highly relevant to neoplastic angiogenesis, invasion, and metastasis. It is not expressed at all or expressed at a very low level on the quiescent endothelium and other normal tissues. Therefore, the integrin  $\alpha_v\beta_3$  receptor may be a promising target in the diagnosis, evaluation, and treatment of malignancies, serving as a tumor-specific agent for single photon emission computed tomography (SPECT).

The tri-peptide sequence of arginine-glycine-aspartic acid (RGD), especially in

cyclic form, has shown high affinity in binding with the receptors of integrin  $\alpha_v\beta_3$ .  $^{99m}\text{Tc}$ -3PRGD2 could be easily prepared and exhibited excellent in vivo behaviors in animal models. No adverse reactions are observed in animal models to date.

For further interest in clinical translation of  $^{99m}\text{Tc}$ -3PRGD2, this study was designed to investigate the value of  $^{99m}\text{Tc}$ -3PRGD2 in assessment of bone metastasis in lung cancer patients, which was compared with  $^{99m}\text{Tc}$ -MDP.

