## Methods

A single dose of 11.1 MBq/kg body weight  $^{99m}\text{Tc}$ -3PRGD2 will be intravenously injected into the patients, and then whole body planar scan (10 cm/min) and chest SPECT imaging (zoom  $\times 1$ , 30 sec/frame/ $6^\circ$ ) will be performed at dual time-points of 1 h and 4 h.  $^{99m}\text{Tc}$ -MDP whole body imaging will be done for comparison within 1 week before or after  $^{99m}\text{Tc}$ -3PRGD2 imaging. Consensus reading of  $^{99m}\text{Tc}$ -3PRGD2 and  $^{99m}\text{Tc}$ -MDP images will be performed on the same workstation by three experienced nuclear medicine physicians blind to the history and pathological diagnosis. The sensitivity, specificity, accuracy, positive predictive value, and negative predictive value will be employed to determine the efficacy of  $^{99m}\text{Tc}$ -3PRGD2 imaging for the diagnosis of bone metastases.

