## Eligibility

### Inclusion Criteria:

1. Males and females,  $\geq 30$  years old
2. Patients suspected with primary lung cancer with thoracic CT
3. The lung cancer will be histologically confirmed or results of histology will be available.
4.  $^{99m}\text{Tc}$ -MDP whole body scan will be performed within 1 week before or after  $^{99m}\text{Tc}$ -3PRGD2 imaging.
5. The bone lesion will be confirmed from at least 2 imaging modalities (SPECT/CT/MRI/ $^{18}\text{F}$ -FDG PET-CT) and 6-month follow-up.

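### The aim is to compare 3PRGD2 with MDP, but the one stated analysis gives accuracy indices for 3PRGD2 alone and does not say whether they are per patient or per lesion

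*Protocol*

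**What the plan says.** The protocol states a comparative purpose three times:

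- Aims: "The aim of this sub-topic was to compare" 3PRGD2 imaging with the MDP bone scan.
- Introduction: the value of 3PRGD2 "in assessment of bone metastasis in lung cancer patients, which was compared with" MDP.
- Methods: MDP "whole body imaging will be done for comparison within 1 week before or after" the 3PRGD2 scan. Three physicians read both sets of images in consensus.

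The analysis is one sentence in Methods: "The sensitivity, specificity, accuracy, positive predictive value, and negative predictive value will be employed to determine the efficacy of" 3PRGD2 "imaging for the diagnosis of bone metastases". MDP does not appear in it.

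On the unit, eligibility is by patient ("Patients suspected with primary lung cancer with thoracic CT") and the size is given as "Estimated Enrollment: 40". Inclusion criterion 5 sets verification for the lesion: "The bone lesion will be confirmed from at least 2 imaging modalities", together with six months of follow-up. The analysis sentence does not say which unit the five indices use.

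**The concern.** A comparison needs an estimate for each tracer and an estimate of the difference. The stated analysis supplies only the first half, for one tracer. The design is paired, since each patient is both case and control for the two scans, and the stated analysis makes no use of that. A trial that followed the sentence exactly could report a good 3PRGD2 sensitivity without showing whether MDP did as well or better in the same patients.

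The open unit adds a second difficulty. Per patient and per lesion, sensitivity answers different questions and has different denominators. Specificity and negative predictive value are affected most, because at lesion level someone must decide which sites count as true negatives. If the choice is made after the images are read, it can favour one tracer.

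**Working it through.** **1. Aim and analysis side by side**

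| Element | Aims, Introduction and scan acquisition | Analysis sentence |
|---|---|---|
| Tracers covered | 3PRGD2 and MDP | 3PRGD2 only |
| Contrast | comparison in the same patients | none stated |
| Unit | patient (eligibility); lesion (confirmation) | none stated |

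The data for a paired comparison are to be collected. Only the analysis sentence falls short of the aim.

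**2. The planned size**

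The figure of 40 cannot be reproduced. The protocol gives no significance level, power, expected accuracy, discordance, prevalence of bone metastasis, lesions per patient or intra-patient correlation. Everything below except N = 40 is therefore an assumption or a property of the test, used for illustration only.

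**3. What the paired patient-level test can show**

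Sensitivity is compared in patients with bone metastasis and specificity in those without, so each comparison uses only part of the 40. The exact two-sided McNemar p-value when all k discordant patients favour the same tracer is 2 × 0.5^k:

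- k = 5: 2 × 0.5^5 = 0.0625
- k = 6: 2 × 0.5^6 = 0.031

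Six is thus the smallest discordant count that can give p<0.05, and then all six must point the same way. With more discordant patients some may go the other way. For example, 8 v 1 gives 2 × (1 + 9)/2^9 = 0.039.

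Assume that 25% of patients with metastasis are detected by 3PRGD2 only and 5% by MDP only. The exact power at two-sided 0.05 is then:

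| Patients with bone metastasis | Power |
|---|---|
| 20 | about 20% |
| 30 | about 40% |
| 40 (everyone positive) | about 57% |

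Single-tracer precision is also limited. An observed sensitivity of 16/20 has an exact 95% interval of 56.3% to 94.3%, and 32/40 has 64.4% to 90.9%.

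**4. What clustering would do to a lesion-level result, if one is reported**

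With m lesions per patient and intra-patient correlation ICC, the design effect is DE = 1 + (m − 1) × ICC. The correct interval is √DE times as wide as one that treats lesions as independent. A nominal 95% interval then covers with probability 2Φ(1.96/√DE) − 1.

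| m | ICC | DE | Width ratio | Coverage of the naive 95% interval |
|---|---|---|---|---|
| 2 | 0.1 | 1.1 | 1.05 | about 94% |
| 5 | 0.3 | 2.2 | 1.48 | about 81% |
| 10 | 0.5 | 5.5 | 2.35 | about 60% |

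With one lesion per patient or an ICC of 0, the ratio is 1.0 and nothing changes.

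**The case against.** The strongest reply is that the protocol plainly intends a comparison: MDP is acquired for that purpose and read by the same physicians. A separate statistical analysis plan may exist, and the choice of test, the interval method and the handling of clustering commonly sit there. That part stands, and the absence of those details is not the point here. What remains is the sentence that the protocol does contain. It limits the accuracy indices to one tracer under a comparative aim and leaves their unit open. Which tracers the indices cover, and per what unit, belongs to the definition of the objective.

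Three stronger readings are tempting, and the document does not support them:

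- A reader might infer that MDP is never evaluated. The protocol does have it read for comparison. What is missing is a stated MDP index and a stated contrast.
- A reader might infer that the planned lesion-level intervals are too narrow. The protocol plans no interval, test or lesion-level analysis. The risk arises only if lesions are pooled as independent and results within a patient are positively correlated.
- A reader might infer that confirming lesions contradicts enrolling patients, or that lesion-level specificity cannot be calculated. A patient-level reference standard also rests on confirmed lesions, and detected lesions shown to be benign can supply negatives. The unit is undefined, but the two passages do not conflict.

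It can also be objected that the proposed patient-level test is weak at this size. The power figures bear that out, and it is a real drawback of the fix.

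**Conclusion.** The point holds in limited form. The one stated analysis does not match the comparative aim and leaves the unit of analysis open. This rests on the protocol's wording alone and needs no assumption. It should be corrected, because it decides whether the trial answers its own question.

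The numerical parts are conditional. The 1.05 to 2.35 widening applies only to a lesion-level analysis that ignores clustering, over the assumed ranges, and cannot be derived from the protocol. The power figures depend on the assumed discordance and number of positive patients. The minimum of six discordant patients is a property of the exact test and depends on no assumption about this trial.

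**What to change.** Rewrite the analysis sentence in Methods so that it:

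1. reports sensitivity, specificity, accuracy, PPV and NPV for both 3PRGD2 and MDP against the same reference standard;
2. names the patient as the primary unit and says how confirmed lesions determine a patient's status;
3. makes the paired differences (3PRGD2 minus MDP) in sensitivity and in specificity the main comparison, each with a paired 95% confidence interval and an exact McNemar test;
4. makes any lesion-level results secondary, states which lesions count as negatives (for example, detected lesions shown to be benign), and clusters the intervals by patient, by GEE or a patient-level bootstrap.

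This costs analysis wording only and uses scans and readings already planned. Scoring a fixed list of skeletal regions would be a larger change: it would need region-level reading and a reference result for negative regions, and it is not required here. The drawbacks are that the paired patient-level comparison will be imprecise with 40 patients and that clustered lesion-level intervals will be wider than naive ones. The report should therefore lead with the estimated differences and their intervals, and should not read a non-significant test as evidence that the tracers are equivalent.

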## Eligibility

### Inclusion Criteria:

1. Males and females,  $\geq 30$  years old
2. Patients suspected with primary lung cancer with thoracic CT
3. The lung cancer will be histologically confirmed or results of histology will be available.
4.  $^{99m}\text{Tc}$ -MDP whole body scan will be performed within 1 week before or after  $^{99m}\text{Tc}$ -3PRGD2 imaging.
5. The bone lesion will be confirmed from at least 2 imaging modalities (SPECT/CT/MRI/ $^{18}\text{F}$ -FDG PET-CT) and 6-month follow-up.

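### Inclusion criterion 5 lets the 3PRGD2 SPECT scan count towards the reference standard it is scored against

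*Protocol*

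**What the plan says.** Protocol, Inclusion Criteria, item 5: "The bone lesion will be confirmed from at least 2 imaging modalities (SPECT/CT/MRI". FDG PET-CT completes the list, and 6-month follow-up is required as well. No other sentence in the protocol says how the true status of a bone lesion is established, so this item serves as the reference standard although it stands among the eligibility criteria.

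Protocol, Methods: "The sensitivity, specificity, accuracy, positive predictive value, and negative predictive value will be employed to determine the efficacy of" 3PRGD2 imaging for bone metastases. MDP "whole body imaging will be done for comparison within 1 week before or after" the 3PRGD2 scan.

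What counts as SPECT in this protocol:
- The Introduction presents the integrin approach as "serving as a tumor-specific agent for single photon emission computed tomography (SPECT").
- Methods acquires a whole body planar scan "and chest SPECT imaging (zoom" and further settings follow), at 1 h and 4 h.
- The Flow Chart has one row labelled SPECT, and it is the 3PRGD2 examination. MDP is called a whole body scan throughout.
- The table of centres lists each machine under the heading SPECT system.

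The three image readers are "blind to the history and pathological diagnosis". The protocol does not say who sets the reference diagnosis or what that person may see.

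**The concern.** An accuracy study needs a reference that is formed independently of the tests being judged. If a positive 3PRGD2 scan can be one of the two results that confirm a lesion, agreement between the test and the reference is partly agreement of the test with itself. This is incorporation bias.

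Two things are at stake. First, all five accuracy measures named in Methods depend on this reference, and apparent sensitivity is the one most readily inflated. Second, the stated aim is a comparison of 3PRGD2 with MDP. If one of the two scans enters the reference for a lesion and the other does not, the comparison is tilted towards the one that enters, whatever the tests' real merits. Reader blinding to history and pathology does not help, because the overlap arises when a scan result is counted and not when it is read.

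**Working it through.** **No figure to reproduce.** The protocol states no expected accuracy, and its enrolment ("Estimated Enrollment: 40") comes without alpha, power or effect size. The check is therefore a reading of the text, followed by an illustration of size.

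**Text.**
1. Item 5 names SPECT as a confirming modality.
2. The only scheduled examination labelled SPECT is 3PRGD2.
3. No sentence excludes the study scans.
4. Methods scores 3PRGD2 for bone metastases, and item 5 is the only rule that says what a bone lesion truly is.

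Following the rule as written, 3PRGD2 may supply one of its own two confirmations.

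**Illustration.** All inputs are assumed and none comes from the protocol: lesion prevalence 0.40; 3PRGD2 and MDP both 0.75/0.85 (sensitivity/specificity); CT 0.75/0.90; MRI 0.85/0.90; results independent given true status. The reference is positive if at least 2 counted modalities are positive and negative otherwise. Follow-up is not modelled.

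CT and MRI results given true status:

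| | both positive | exactly one positive | both negative |
|---|---|---|---|
| Metastasis | 0.75 × 0.85 = 0.6375 | 0.75 × 0.15 + 0.25 × 0.85 = 0.325 | 0.25 × 0.15 = 0.0375 |
| No metastasis | 0.10 × 0.10 = 0.01 | 2 × 0.10 × 0.90 = 0.18 | 0.90 × 0.90 = 0.81 |

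*Reference A: at least 2 of 3PRGD2, CT and MRI.*
- P(reference positive | metastasis) = 0.6375 + 0.325 × 0.75 = 0.88125; P(reference positive | none) = 0.01 + 0.18 × 0.15 = 0.037.
- P(reference positive) = 0.4 × 0.88125 + 0.6 × 0.037 = 0.3747; P(reference negative) = 0.6253.
- 3PRGD2 and reference both positive: 0.4 × 0.75 × (0.6375 + 0.325) + 0.6 × 0.15 × (0.01 + 0.18) = 0.30585. Apparent sensitivity = 0.30585 / 0.3747 = 0.816.
- 3PRGD2 and reference both negative: 0.4 × 0.25 × (0.325 + 0.0375) + 0.6 × 0.85 × (0.18 + 0.81) = 0.54115. Apparent specificity = 0.54115 / 0.6253 = 0.865.
- MDP and reference both positive: 0.4 × 0.75 × 0.88125 + 0.6 × 0.15 × 0.037 = 0.267705. Apparent sensitivity = 0.267705 / 0.3747 = 0.714.
- MDP and reference both negative: 0.4 × 0.25 × 0.11875 + 0.6 × 0.85 × 0.963 = 0.503005. Apparent specificity = 0.503005 / 0.6253 = 0.804.

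Two identical tests thus differ by about 10 points in sensitivity and 6 in specificity.

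*Reference B: CT and MRI only, both required positive, everything else scored negative.* P(reference positive) = 0.4 × 0.6375 + 0.6 × 0.01 = 0.261.
- Sensitivity, either test: (0.255 × 0.75 + 0.006 × 0.15) / 0.261 = 0.736.
- Specificity, either test: (0.4 × 0.25 × 0.3625 + 0.6 × 0.85 × 0.99) / 0.739 = 0.54115 / 0.739 = 0.732.

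The tests are level again, but specificity is well below the true 0.85, because CT and MRI disagree on 0.4 × 0.325 + 0.6 × 0.18 = 0.238 of lesions and all of these were scored negative.

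*Reference C: as B, with disagreements set aside as unverified.* Reference negatives are 0.4 × 0.0375 + 0.6 × 0.81 = 0.501. Specificity, either test: (0.015 × 0.25 + 0.486 × 0.85) / 0.501 = 0.832. Sensitivity stays at 0.736.

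**Other assumed values.** With CT, MRI and PET each 0.80/0.90, MDP 0.85/0.70, 3PRGD2 from 0.60/0.80 to 0.80/0.90 and prevalence 0.2 to 0.5, the reference was moved from at least 2 of CT, MRI and PET to at least 2 of CT, MRI and 3PRGD2. Apparent 3PRGD2 sensitivity rose by about 0.07 to 0.16 and specificity by about 0.03 to 0.07. MDP changed by about −0.04 to 0.00 in both.

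**The case against.** The strongest reply is that the rule can be met without either study scan: CT plus MRI plus follow-up satisfies item 5. That stands. The text permits incorporation and does not impose it, so a reader who infers that the study scans do define the truth, or that the results will be biased, goes further than the document.

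A reader might also infer that MDP is in the same position as 3PRGD2. The protocol never calls MDP a SPECT examination; only the heading over the machines suggests it. A scenario in which MDP and CT together form the reference (apparent sensitivity 1.00 for MDP against 0.727 for an identical 3PRGD2) is therefore inference and should not be cited as the size of the problem. A sensitivity of 100% by construction likewise assumes that confirmed means positive on both scans and that everything else is negative. Item 5 says neither. Nor is every measure inflated: when the test and CT must both be positive, the included test's specificity falls from 0.85 to 0.80.

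Follow-up is mandatory and may reject lesions that are falsely positive on both scans. This should lessen the bias. It does not remove SPECT from the imaging half of the rule, and no criterion for reading follow-up is given.

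Read strictly, 3PRGD2 SPECT covers only the chest, which would confine the problem to thoracic lesions, but the Flow Chart labels the whole examination SPECT. If SPECT/CT is read as one hybrid modality, a SPECT image still enters the reference.

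Finally, an analysis plan that is not shown may deal with adjudication and blinding, so their absence here is not the point. The point is that the protocol expressly lists SPECT as confirmatory.

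**Conclusion.** The concern holds in a limited form. The protocol's only rule for bone-lesion truth permits the 3PRGD2 index test, and by inference the MDP comparator, to count as one of the two confirming modalities. This can inflate the apparent sensitivity of 3PRGD2 and tilt the comparison when only one of the two scans is counted.

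The size cannot be derived from the documents. In the illustration, a true 75%/85% appears as 82%/87% for the test inside the reference and 71%/80% for an identical test outside it. These figures rest on assumed accuracies, an assumed prevalence and conditional independence, and they leave out the 6-month follow-up. They show direction and plausible order only. The point still merits correction before analysis, because every accuracy measure in Methods depends on this one sentence.

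**What to change.** Amend item 5 to say that neither 3PRGD2 nor MDP images count as confirming modalities. Keep the rest of the standard: at least 2 of CT, MRI and FDG PET-CT, and 6-month follow-up. Follow-up should stay mandatory; making it an alternative to a second modality would weaken a safeguard the protocol already has. State that the reference diagnosis is set without access to the 3PRGD2 and MDP results.

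Report lesions that lack two non-study modalities as unverified and do not score them negative. The comparison of references B and C shows why: scoring unresolved lesions as negative lowers apparent specificity for both tests. Keep the SPECT-inclusive definition as a sensitivity analysis.

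The change to the text is a few sentences. The real cost is lost lesions. The Flow Chart lists CT, MRI and PET/CT at V1 but does not say that every patient has all three or that they cover the skeleton, and inclusion item 2 mentions only thoracic CT. How many lesions become unverified cannot be estimated from the protocol. With 40 patients planned, precision may fall, the verified lesions may be a selected group, and the figures may look less favourable.

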### Exclusion Criteria:

1. Females planning to bear a child recently or with childbearing potential
2. Known severe allergy or hypersensitivity to IV radiographic contrast
3. Inability to complete the needed examination due to severe claustrophobia, radiation phobia, etc.
4. Concurrent severe and/or uncontrolled and/or unstable other medical disease

that, in the opinion of the investigator, may significantly interfere with compliance

### Flow Chart

| RESEARCH PROCESS                         | V1 | V2                                  | V3                                                                 | V4
(Surgery) | V5
(Follow-up) |
|------------------------------------------|----|-------------------------------------|--------------------------------------------------------------------|-----------------|-------------------|
| Window period                            |    | Within two weeks before the surgery | Within one week before/after the $^{99m}\text{Tc}$ -3PRGD2 imaging |                 | Every 3-6 months  |
| Inclusion / Exclusion criteria           | X  |                                     |                                                                    |                 |                   |
| Signed the Informed Consent              | X  |                                     |                                                                    |                 |                   |
| Medical history / Concomitant diseases   | X  |                                     |                                                                    |                 |                   |
| CT, MRI, PET/CT                          | X  |                                     |                                                                    |                 |                   |
| Tumor markers and other laboratory tests | X  |                                     |                                                                    |                 |                   |
| $^{99m}\text{Tc}$ -3PRGD2 SPECT          |    | X                                   |                                                                    |                 |                   |
| $^{99m}\text{Tc}$ -MDP whole body scan   |    |                                     | X                                                                  |                 |                   |
| Adverse events                           |    | X                                   |                                                                    |                 |                   |
| Surgical records and pathology results   |    |                                     |                                                                    | X               |                   |
| Preserve specimens                       |    |                                     |                                                                    | X               |                   |
| Subsequent treatment and follow-up       |    |                                     |                                                                    |                 | X                 |

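### Adverse events are scheduled for recording only at V2, with no stated window, although later post-dose contacts already exist and the only tracer safety evidence cited is from animals

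*Protocol*

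**What the plan says.** The Flow Chart has five visits, V1 to V5. The row "Adverse events" is marked once, under V2, which is also where the 99mTc-3PRGD2 SPECT is marked. The cells for V3, V4 and V5 in that row are blank.

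The later contacts are these:

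- **V3** is the 99mTc-MDP scan. The Methods say that it "will be done for comparison within 1 week before or after" the 3PRGD2 imaging.
- **V4** is surgery. The Flow Chart places V2 "Within two weeks before the surgery". V4 collects surgical records, pathology and specimens.
- **V5** is follow-up, "Every 3-6 months", and its content is "Subsequent treatment and follow-up". Inclusion criterion 5 relies on at least two imaging modalities "and 6-month follow-up" to confirm bone lesions.

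On the tracer's safety, the Introduction says only that "No adverse reactions are observed in animal models to date". The protocol text gives no adverse-event window, no telephone check and no later enquiry.

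**The concern.** The Introduction presents the study as a step in bringing the tracer into clinical use and cites no human safety data. In that setting, one would expect adverse-event enquiry to extend beyond the dosing visit, at least at contacts that take place anyway. As scheduled, a site has no instruction to ask about, or log, a reaction that begins after V2.

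What is at stake is the safety information. Any statement that no adverse events occurred would hold for V2 alone and could be read as covering more. A statistical analysis plan cannot repair this, because it can summarise only what was collected. Sensitivity, specificity, accuracy and the predictive values do not depend on it.

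**Working it through.** The protocol gives no adverse-event rate, window or safety sample-size argument, so there is no figure to reproduce. The check sets the visit schedule against the time of dosing, followed by an illustration on assumed rates.

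**Step 1. Which visits follow the injection?** The injection is at V2.

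| Visit | Timing relative to V2 | Always post-dose? | Adverse-event mark |
|---|---|---|---|
| V2 | day of injection | – | yes |
| V3 | up to 1 week before or after | no, only if the MDP scan comes second | no |
| V4 | up to 2 weeks after | yes, in patients who have surgery | no |
| V5 | every 3–6 months | yes | no |

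One of five visits is marked.

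**Step 2. What is the earliest later contact for each patient?**

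- MDP scan second: V3, at most 7 days after V2 (V4 could come sooner in patients who have surgery).
- MDP scan first, with surgery: V4, at most 14 days after V2.
- MDP scan first, no surgery: the first V5, on the 3–6 month schedule.

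The protocol does not say how many patients fall in each group. Every patient has some later contact, but it is early only in the first two groups.

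**Step 3. How much could be lost? (illustration only)** Take N = 40 (Estimated Enrollment). Let p be the true proportion of patients with a reaction and f the share of reactions that start after V2. Both p and f are assumptions; neither is in the documents.

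- Chance of recording at least one event, V2 only: 1 − (1 − p(1 − f))^40
- Same, with complete capture at later contacts: 1 − (1 − p)^40

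Example, p = 5% and f = 50%: V2 only, 1 − 0.975^40 = 63.7%; complete capture, 1 − 0.95^40 = 87.1%.

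| Assumed p | V2 only, f = 25% | V2 only, f = 50% | V2 only, f = 75% | Complete capture |
|---|---|---|---|---|
| 1% | 26.0% | 18.2% | 9.5% | 33.1% |
| 2% | 45.4% | 33.1% | 18.2% | 55.4% |
| 5% | 78.3% | 63.7% | 39.5% | 87.1% |
| 10% | 95.6% | 87.1% | 63.7% | 98.5% |

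If f = 0, the V2-only column equals complete capture and nothing is lost. If f = 100%, V2-only collection records no reaction at any p. The loss therefore depends on f, about which the documents are silent.

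**Step 4. What a zero count would mean.** With 0 events in 40 patients, the one-sided 95% upper limit is 1 − 0.05^(1/40) = 7.2%. That limit comes from N = 40 and is the same under either schedule, so it does not measure the gap. The schedule changes what the limit refers to: with V2-only collection, reactions apparent at V2.

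**The case against.** Recording adverse events at the visit of a single injection is internally consistent. Nothing is miscalculated or contradicted. Safety is not among the aims, and the Methods list only accuracy measures, so no safety claim is planned. The study is part of a larger multi-center study whose safety arrangements cannot be seen here. Later contacts are also imperfect: V3 may come before dosing, V4 is confounded by the operation, and at a V5 months later an event is hard to link to one injection. All of this stands, and it keeps the point minor. It does not explain why contacts that take place anyway carry no adverse-event mark.

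Three stronger readings are tempting, and the documents do not support them:

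- **That observation stops about 4 hours after injection.** The Methods say that imaging "will be performed at dual time-points of 1 h and 4 h". Those are imaging times. The length of the adverse-event period at V2 is not stated.
- **That nothing at all could be learned about later events.** A late event might surface at V5 under "Subsequent treatment and follow-up", although nothing requires it to be logged as an adverse event. What is absent is scheduled, systematic recording.
- **That delayed reactions are in fact being missed.** No passage shows that they occur. The schedule is simply not set up to record them if they do.

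**Conclusion.** The point holds as a minor weakness of the schedule. Adverse-event recording is fixed at V2 alone, with no stated duration, for a tracer whose only cited safety evidence is from animals. Reactions that start later are not scheduled for systematic recording, and a finding of no adverse events would be limited to V2.

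The size of the loss cannot be derived from the protocol. It ranges from nothing, if all reactions appear at V2, to every reaction, if all are delayed. The conclusion assumes that the Flow Chart is the complete schedule for this sub-study and that the parent study adds no safety follow-up. The accuracy comparison with 99mTc-MDP is unaffected.

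**What to change.** In the adverse-events row of the Flow Chart, add a mark:

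- at V3, when it follows V2;
- at V4, before the operation;
- at the first V5 contact, for patients with no earlier post-dose contact.

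State the period that the V2 mark covers. Record the onset time of each event relative to the 3PRGD2 injection, so that events before and after surgery or new treatment can be reported separately. Any summary of adverse events should name the contacts that it covers.

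The cost is a few form entries at contacts that already exist, with no new visit and no change to the accuracy analysis. The drawback is harder attribution once surgery or new treatment has begun, and weak recall in patients whose first later contact is V5. Onset time eases the first problem but does not remove it.
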